### Data analysis strategy

The analytical framework of this study is structured to evaluate three outcomes: (a) trait-level directional movement, (b) state-level micro-trajectory change, and (c) mechanism enactment evidence. These three analytical layers correspond directly to the theoretical dimensions the intervention engages in disposition, enactment, and meaning-in-use. To assess trait-level shifts, pre- and post-intervention changes in the BSCS and SSBS will be quantified using a within-subject standardized mean difference, following Lakens’s (2013) generalized within-subject effect size formulation. This approach mitigates dependence on between-subject variability and is appropriate for feasibility designs wherein each participant serves as their own baseline control (Lakens, 2013, 2017). To robustly index the magnitude of directional movement, 95% confidence intervals will be calculated, despite traditional null-hypothesis significance testing not being required under feasibility logic.

State-level EMA sequences (Phase A baseline vs. Phase B intervention) will be analyzed using Tau-U with baseline trend correction. Importantly, correcting for baseline trend prevents inflated effect-size estimates that might otherwise be misattributed to intervention exposure rather than pre-existing directional drift. Tau-U allows non-overlap evaluation even with small samples and is currently the most methodologically defensible effect-size metric for SCED micro-regulation sequences. Qualitative data will be evaluated via reflexive thematic analysis, though explicitly restricted to mechanism verification rather than narrative phenomenology. Coding will be deductive and anchored to the weekly objective architecture.

Finally, to integrate the three evidence streams, a triangulation matrix will be constructed to map (a) trait-level shifts, (b) state-level effect estimates, and (c) qualitative mechanism evidence. The purpose of this synthesis is not to blend subjective narrative with statistical data, but to evaluate whether the targeted mechanism signal is reliably detectable across heterogeneous measurement modes. Methodological convergence across these domains confirms intervention feasibility, while signal divergence indicates a structural implementation malfunction.

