### Model definition

The model is conceptualized as a developmental delivery architecture wherein human counselors establish the relational frame and developmental arc, while AI system executes the high-frequency micro-dosage required for proximal skill enactment. Critically, this intervention does not conceptualize AI as a counselor analog, therapist substitute, or diagnostic component, but as a systemic dosage amplifier. Counselors maintain primary responsibility for relational containment, while the AI autonomously delivers the high-volume, micro–developmental practice opportunities that human counselors cannot feasibly scale. This approach is grounded in the developmental reality that self-regulation and social connectedness are not cultivated through episodic learning, but through continuous, real-world repetition. The architecture therefore mirrors the mechanisms of motor-skill acquisition: micro-practice → consolidation → transfer. This counselor–AI co-delivery framework makes this repetition feasible within standard school constraints.

The intervention is deployed throughout eight consecutive school weeks. Each week focuses on one thematic developmental objective (see Table 1) and offers a synchronous 10–15-min counselor mini-session. This mini session serves as a vital “anchor point,” grounding the week’s developmental target in a supportive relational context while allowing the counselor to check ecological fit, safety, and progress. The remainder of the weekly dosage is delivered digitally through daily MI-style micro-nudges (e.g., ≤ 40 words). The sequence is intentionally graded to build capacity over time: initial weeks emphasize foundational awareness and micro-choice recognition; intermediate weeks prioritize active skill application in real-life contexts; final weeks focus on value mapping, identity congruence, and future transfer. In essence, the intervention is paced not by superficial “topic rotation,” but through the cumulative scaffolding of practice complexity.

**Table 1 tab1:** Structured eight-week progression of developmental objectives and measurable indicators.

Week	Theme	Weekly skill focus	Measurable outcome wording	Measurement schedule
0				Weeks −2 to −1: Consent, demographics, BSCS/SSBS (pre), two-week daily EMA baseline (Phase A)
1	Awareness	Noticing internal states & situational triggers	Student(s) can label at least one emotional state + one situational trigger per day	

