## Method

### Setting and participants

The intervention is designed for implementationwithin mainstream high school counseling settings serving adolescents aged 14–18. This ecological frame is intentional. As a feasibility study, the sample size is determined by the need to evaluate implementation applicability and estimation precision rather than statistical power for clinical efficacy. A target sample of 40–60 students from routine school caseloads, is sufficient to yield narrow confidence intervals (CIs) for recruitment/retention/compliance and to visualize heterogeneous individual-level micro-trajectories within an authentic delivery context. Feasibility will be evaluated against four pre-specified operational thresholds: (a) a recruitment rate ≥ 70% of eligible students; (b) a retention rate of ≥ 80% (defined as completing both pre- and post-intervention trait measures); (c) a median EMA compliance of ≥ 60% for daily prompts (1–7 Likert scale) across Weeks 1–8; (d) an intervention fidelity of ≥ 75% (defined as weeks where all three checklist items are met). These thresholds were derived from established benchmarks in the feasibility and pilot trial literature (Billingham et al., 2013; Eldridge et al., 2016). The 70% recruitment and 80% retention rates are widely adopted as minimum indicators of a viable study pipeline for a subsequent full-scale trial. The 60% EMA compliance threshold reflects the empirically observed lower bound of acceptable ecological momentary data completeness in adolescent digital health studies (Shiffman et al., 2008); compliance below this level produces phase lengths insufficient for reliable Tau-U estimation. The 75% fidelity threshold is grounded in the intervention science literature’s recommendation that at least three-quarters of protocol sessions be delivered as specified before efficacy conclusions can be considered (Bellg et al., 2004). Together, these benchmarks ensure that a positive feasibility verdict is substantively meaningful rather than nominally so.

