Momentary (state-level) regulations will be assessed through a daily, single-item Ecological Momentary Assessment (EMA) self-rating prompt delivered throughout the eight-week intervention phase. Adolescents are prompted with the question: “Right now, how effectively are you managing your emotions and behavior?” and respond on a 1–7 Likert scale (1 = *not effectively at all*, 7 = *very effectively*). Basically, this item is designed to capture real-time regulatory enactment rather than a retrospective or global self-assessment. Thus, EMA state trajectories recorded across Phase B provide a mechanism-level time-series dataset optimally structured for single-case Tau-U analysis.

All outcome indicators depend on student self-report, the protocol also incorporates two additional informant-based measures. Teacher behavioral ratings will be collected at pre- and post-intervention timepoints using a brief four-item adaptation of the Social Skills Improvement System (SSIS; Elliott et al., 2008) targeting observable classroom regulation behaviors (e.g., “This student recovers quickly from frustration”) and prosocial conduct (e.g., “This student initiates positive interactions with peers”). Items are rated on a 4-point frequency scale (1 = never, 4 = almost always) by the student’s primary classroom teacher. Parent or guardian reports will be collected using a parallel four-item brief form targeting home-context regulation and social behavior, administered via a secure online survey link at the same two timepoints. These informant sources provide convergent evidence from ecologically distinct observational contexts, reducing the sole reliance on student self-report and mitigating single-source inflation of perceived effects.

Implementation of fidelity will be captured via weekly counselor fidelity summaries. To minimize administrative burden and avoid interpretive drift, this documentation uses a structured, three-item binary checklist. The counselor simply records whether: (1) micro-nudges were opened at least four times during the week; (2) the student submitted at least one reflective note; and (3) the student concretely described at least one pro-social or regulation-aligned behavior. Counselors may optionally add a single-sentence contextual remark if relevant. These logs do not serve as qualitative data for phenomenology, but rather as direct fidelity evidence confirming that the designed mechanism was actively enacted.

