Quantitatively, the design combines a within-subject trait-level pre–post comparison with an embedded single-case AB probe. The sequence consists of a pre-intervention baseline (Phase A; Weeks −2 and −1) and an active intervention period (Phase B; Weeks 1–8). The two-week baseline was adopted. A minimum of 10 data points in Phase A provides a more stable trend estimate for Tau-U baseline correction and more clearly distinguishes pre-existing directional drift from intervention-related change. Throughout Phase B, state-level EMA micro-ratings (1–7 Likert scales) index continuously index momentary regulation states. Trait-level self-regulation and social connectedness are measured at pre- and post-intervention timepoints via the within-subject standardized mean difference (Cohen’s *d*). To rigorously capture the dynamics of the state-level micro-trajectories, data will be evaluated using Tau-U, a robust, best-practice non-overlap effect size optimized for AB sequences in single-case experimental design (SCED) methodology.

The qualitative strand consists of (a) weekly counselor fidelity logs and (b) brief, one-sentence reflective student notes. These materials are not narrative interviews; rather, they serve as real-time process-evidence. Therefore, the analytic objective is not to achieve thematic saturation, but to execute mechanism-alignment detection. Reflexive thematic analysis will be used to identify and verify whether developmental practice indicators outlined in Table 1 occurred within a real-world educational environment.

All reflective notes remain accessible to the counselor to preserve the core ethical principle of human relational containment. The AI system does not store raw text beyond the generation of summary logs. Data retention adheres strictly minimal-retention feasibility norms; export functions are disabled. No participant data or conversational data is used for model training or model improvement. Furthermore, no algorithmic action is permitted without the possibility of immediate human override; should emotional dysregulation signals emerge, counselors escalate the case in accordance with established institutional safeguarding protocols. In this design, the AI is never the locus of clinical decision; rather, it is the engine for prompt density. Human counselors retain absolute safeguarding authority and interpretive control.

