#### Missing data handling

Missing data for the trait outcomes (BSCS, SSBS), analyses will be managed via pairwise availability with sensitivity checks using last-observation-carried-forward for descriptive ranges. For the state-levelEMA data, missing days will simply be omitted because Tau-U inherently tolerates unequal phase lengths and missing data points within time-series sequences. To rigorously assess the effect of intervention dosage, per-participant compliance (percentage of EMA prompts answered) will be reported and descriptive contrasts comparing high- compliance (≥ 60%) versus low- compliance (< 60%) will be conducted.

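### With a two-week baseline and an eight-week intervention phase, the Tau-U trend correction removes little of any pre-existing drift, so the statement that it prevents drift inflation does not hold

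*Protocol article*

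**What the plan says.** The Research design section sets the phases: "The sequence consists of a pre-intervention baseline (Phase A; Weeks −2 and −1) and an active intervention period (Phase B; Weeks 1–8". Table 1 describes a "two-week daily EMA baseline (Phase A", and the Measures section a "daily, single-item Ecological Momentary Assessment (EMA) self-rating prompt delivered throughout the eight-week intervention phase". The documents do not say whether daily means calendar days or school days.

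The Data analysis strategy section names the index: "State-level EMA sequences (Phase A baseline vs. Phase B intervention) will be analyzed using Tau-U with baseline trend correction". It then states without qualification what the correction achieves: "correcting for baseline trend prevents inflated effect-size estimates that might otherwise be misattributed to intervention exposure rather than pre-existing directional drift". The Research design section adds that "A minimum of 10 data points in Phase A provides a more stable trend estimate for Tau-U baseline correction", and that this helps to tell drift from intervention-related change.

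Two further rules decide how many ratings enter the index. The feasibility threshold is "a median EMA compliance of ≥ 60% for daily prompts (1–7 Likert scale) across Weeks 1–8", and under Missing data handling "missing days will simply be omitted because Tau-U inherently tolerates unequal phase lengths and missing data points within time-series sequences".

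The Data analysis strategy section also enters the state-level estimate into a triangulation matrix, in which agreement between the evidence streams is taken to confirm feasibility. The Limitations section says that changes cannot be attributed causally and that state-level shifts may reflect maturation or school-calendar effects.

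**The concern.** The baseline correction in Tau-U subtracts a count of trend pairs inside Phase A from a count of pairs between the phases. It does not extrapolate the baseline trend through Phase B. When Phase B is four times as long as Phase A, there are many between-phase pairs and few baseline pairs, so the subtraction is small however strong the trend is. A student whose ratings were already rising before Week 1 would keep nearly the whole Tau-U value after correction.

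Tau-U is the only planned effect estimate for the state layer, and that is the only quantitative layer with a baseline series. A value labelled as trend-corrected, beside a sentence saying that drift inflation is prevented, invites more trust than the index can carry. The article also offers itself as a blueprint for later trials, so the statement is likely to be reused.

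**Working it through.** **Inputs.** From the article: Phase A of 2 weeks, Phase B of 8 weeks, one rating a day on a 1–7 scale, missing days dropped, and a 60% compliance threshold for Weeks 1–8. Planned counts are 14 and 56 on calendar days (2 × 7, 8 × 7) or 10 and 40 on school days (2 × 5, 8 × 5). At 60%, Phase B has about 34 (0.6 × 56 = 33.6) or 24 (0.6 × 40) ratings. The article gives no figure for the size of the correction, so there is none to reproduce.

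**Formula (assumed, because the article does not print one).** Let S_AB be rising minus falling pairs between phases, and S_A the same count within Phase A. Then

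Tau-U = (S_AB − S_A)/(nA·nB) = Tau_AB − [(nA − 1)/(2·nB)]·Tau_A.

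S_A cannot exceed nA(nA − 1)/2, so the largest possible subtraction is (nA − 1)/(2·nB). For a noise-free monotone drift with no intervention effect, Tau_AB = Tau_A = 1, and the corrected value is 1 minus that cap.

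| nA / nB | Cap | Pure drift after correction |
|---|---|---|
| 14 / 56, calendar days | 13/112 = 0.116 | 0.884 |
| 10 / 40, school days | 9/80 = 0.1125 | 0.888 |
| 10 / 56, stated minimum baseline | 9/112 = 0.080 | 0.920 |
| 8 / 34, 60% in both phases | 7/68 = 0.103 | 0.897 |
| 14 / 34, full baseline, 60% in Phase B | 13/68 = 0.191 | 0.809 |
| 10 / 24, full baseline, 60% in Phase B | 9/48 = 0.188 | 0.813 |
| 14 / 24, extreme mix of day counts | 13/48 = 0.271 | 0.729 |

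Direct pair counting on a straight line gave the same 0.884 and 0.888.

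**Other forms of Tau-U.** With Phase A pairs also in the denominator, pure drift gives (784 − 91)/(784 + 91) = 0.79 for 14/56 and (400 − 45)/(400 + 45) = 0.80 for 10/40. With the Phase B trend added, it gives 0.92 to 0.93.

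**With noise.** Assumptions, none of them from the article: start at 3.5, independent noise with SD 1, rounding to 1–7, one straight-line drift through both phases, no intervention effect, 2,000 series per setting.

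| Drift over 10 weeks | 14/56 uncorrected → corrected | 10/40 uncorrected → corrected |
|---|---|---|
| 1 point | 0.258 → 0.254 | 0.266 → 0.262 |
| 2 points | 0.476 → 0.468 | 0.472 → 0.463 |
| 3 points | 0.636 → 0.623 | 0.631 → 0.618 |

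The share removed runs from 0.004/0.266 = 1.5% to 0.013/0.631 = 2.1%. The reason is simple. With 1 point of drift over 70 days, ratings move only 13/69 = 0.19 points within Phase A, so the baseline trend is hard to see. The phase midpoints (days 6.5 and 41.5, counting from 0) differ by 35/69 = 0.51 points.

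**A residualised Tau**, which removes a Theil–Sen baseline slope from the whole series, is not bound by the cap. In 300 series per setting at 14/56 it averaged 0.169 (SD 0.465) for 1 point of drift and 0.337 (SD 0.614) for 3 points. It removed only part of the drift and was very variable.

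**The case against.** Several points on the other side stand.

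- **The Limitations section covers the consequence.** A reader might infer that the article presents drift as ruled out, or makes a causal claim. It does not: it names maturation and school-calendar effects as possible explanations of state-level shifts. That section does not mention the correction, however, and leaves the specific statement in place. The two passages pull against each other.
- **No numerical criterion uses Tau-U.** A reader might infer that the feasibility decision turns on it. The four pre-specified thresholds are recruitment, retention, EMA compliance and fidelity. Tau-U enters only through the triangulation matrix, for which no cut-off is stated.
- **The cap of about 0.12 is not a fixed maximum.** It holds for the subtraction index at the planned lengths. The compliance threshold applies to Weeks 1–8 only, so a fuller baseline and a thinner Phase B raise the cap to about 0.19, or 0.27 in an extreme mix. The article prints no formula, so the bound is conditional on the standard index, which is the natural reading of the name.
- **The ten-point sentence in Research design is comparative.** More baseline ratings do give a steadier trend estimate. It is not wrong in itself; it just does not make the correction larger.
- **Drift size and noise are assumed**, and 0.88 is a noise-free extreme, not an expected bias.

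It is also tempting to conclude that a piecewise mixed model should replace Tau-U. That does not follow. In checks with no intervention effect, a quadratic drift of 1 SD produced a false slope change of about 0.81 SD over 8 weeks. A real but gradual effect produced a zero step, and the article describes an intervention that builds gradually. The slope change is also imprecise: with noise SD 1 and 50 students its standard error is about 0.53 SD per 8 weeks. No model fully separates drift from effect in an uncontrolled AB design.

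**Conclusion.** The statement is wrong as written for this design. At the planned phase lengths the standard correction can lower Tau-U by no more than 0.11 to 0.12, or about 0.19 with a full baseline and 60% Phase B compliance. Pure drift still leaves about 0.88 (0.81 in the uneven case), and under the assumed noisy linear drift about 98% of the artefact remains. The cap is algebra on the article's own phase lengths, given the standard index; the 2% figure depends on the assumed drift and noise. The other forms of Tau-U tried do not rescue the claim, and the residualised Tau does so only in part and with large variability.

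The consequence is limited but real. No threshold and no causal claim depends on Tau-U, but a drift-driven value could count as a converging signal in the triangulation matrix under a label that overstates its protection.

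**What to change.** In the Data analysis strategy section:

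- Delete the claim of prevention. State that, with a two-week baseline and an eight-week intervention phase, the correction removes little of any drift, and refer to the Limitations section.
- For each student, report uncorrected Tau-U, corrected Tau-U and the Phase A trend together, as descriptive quantities not protected against drift.
- In the triangulation matrix, do not count a positive Tau-U alone as a mechanism signal.

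The cost is a few sentences and two more reported quantities per student, all from data already planned.

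Optionally, as a supplementary analysis only, fit a multilevel piecewise model to the EMA series and report both the step at Week 1 and the slope change with 95% confidence intervals. State that it assumes linear drift, that the slope change is imprecise with a two-week baseline, and that it cannot separate curved drift from a gradual effect. The added cost is one mixed model and the text needed to state those limits.

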### Limitations

Given its architecture as a feasibility design, this study cannot causally attribute observed changes to the intervention, nor does it make any statistical inference regarding comparative superiority or clinical efficacy. Any observed trait- or state-level shifts may be confounded by normative developmental maturation, placebo engagement, social desirability, technological novelty effects, or seasonal artifacts of the school calendar. Furthermore, the fidelity documentation is strictly designed to assess the mere presence of mechanism enactment, not the qualitative depth or mastery of the skill. Consequently, no estimates of generalizability are proposed or assumed.

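### The protocol gives two rules for the feasibility verdict, with no order between them, and the triangulation rule can label a soundly delivered programme a malfunction

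*Protocol article*

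**What the plan says.** In the Protocol article, Setting and participants, the rule is: "Feasibility will be evaluated against four pre-specified operational thresholds". These are recruitment of at least 70% of eligible students, retention of at least 80%, median EMA compliance of at least 60%, and fidelity of at least 75%. The section closes by saying that these benchmarks are what give a positive verdict its substance.

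The Data analysis strategy sets up a triangulation matrix with three streams: trait-level change, state-level effect estimates and qualitative evidence of the mechanism. It ends: "Methodological convergence across these domains confirms intervention feasibility, while signal divergence indicates a structural implementation malfunction". Neither term is defined, and the four thresholds are not mentioned.

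Three other statements bear on this rule:

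- Theoretical grounding: positive youth development indicators are not all equally responsive to short exposure in school.
- Measures: the BSCS captures enduring differences between people.
- Limitations: trait or state "shifts may be confounded by normative developmental maturation, placebo engagement, social desirability, technological novelty effects", or by the school calendar.

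**The concern.** One verdict has two rules that use largely different data, so they can disagree. A school could meet all four thresholds and still be recorded as an implementation failure because a trait scale did not move with the daily ratings. In the other direction, the three streams could agree while a threshold is missed, and the text does not say what is then concluded.

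The verdict on implementation is the study's main purpose, and the protocol is offered as a template for later randomised trials. With convergence undefined and no order between the rules, the verdict could be settled after the data are seen.

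**Working it through.** **The two rules side by side.** The protocol gives no operating characteristic for the matrix, so there is no figure to reproduce.

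| | Thresholds (Setting and participants) | Matrix (Data analysis strategy) |
|---|---|---|
| Inputs | Recruitment, retention, EMA compliance, fidelity | BSCS/SSBS change, Tau-U, qualitative evidence |
| Criterion | Numerical | Not defined |
| Positive result | Feasible | Feasibility confirmed |
| Negative result | Threshold missed | Malfunction |
| Precedence | Not stated | Not stated |

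The matrix contains no recruitment, retention or compliance rate. The one overlap is the counselor fidelity logs, which feed both the fidelity threshold and the qualitative strand.

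**Does divergence indicate faulty delivery?** A scale of stable disposition may not move in eight weeks while daily ratings and prompted notes do. The protocol's statements on differing sensitivity predict this without any fault in delivery.

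**Does agreement indicate implementability?** Maturation, social desirability or novelty can move the self-report streams together, as the Limitations allow. Agreement can therefore arise for reasons unrelated to delivery.

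**How often would sampling error alone produce divergence?** Inputs:

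- Completers: the target is 40–60 students. At 80% retention, 0.80 × 40 = 32 and 0.80 × 60 = 48.
- Assumed, not in the documents: three quantitative signals (BSCS, SSBS, group mean Tau-U) as normal z-scores with mean d√n and variance 1, common correlation ρ from 0 to 0.5, and d = 0.2 on each. The qualitative stream is left out.
- Two readings of a signal: the sign of the estimate, or a 95% CI excluding zero on the side of improvement (z > 1.96).

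At ρ = 0 the result follows by hand. With p the chance that one signal is present, P(diverge) = 1 − p³ − (1 − p)³.

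- Sign, n = 32: 0.2√32 = 1.131; p = Φ(1.131) = 0.871; 1 − 0.661 − 0.002 = 0.337.
- Sign, n = 48: 0.2√48 = 1.386; p = 0.917; 1 − 0.771 − 0.001 = 0.228.
- CI, n = 32: p = 1 − Φ(1.96 − 1.131) = 0.204; 1 − 0.008 − 0.505 = 0.487.
- CI, n = 48: p = 1 − Φ(1.96 − 1.386) = 0.283; 1 − 0.023 − 0.369 = 0.608.

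Simulation with 400,000 draws reproduces these to within 0.001 and extends them to ρ = 0.5:

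| Assumed effects (trait / state) | Reading | Diverge, n = 32 | Diverge, n = 48 |
|---|---|---|---|
| 0.2 / 0.2 | Sign | 0.25–0.34 | 0.18–0.23 |
| 0.2 / 0.2 | CI | 0.34–0.49 | 0.42–0.61 |
| 0 / 0.5 | Sign | 0.66–0.75 | 0.67–0.75 |
| 0 / 0.5 | CI | 0.81–0.82 | 0.93–0.94 |

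The last two rows show the case that the protocol's sensitivity argument points to: state ratings move and trait scales do not. Delivery quality enters none of these calculations.

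**The case against.** The strongest defence is that the matrix only corroborates. The thresholds are said to be what makes a positive verdict meaningful, and nothing in the Data analysis strategy overrides them. This stands in part. A reader might infer that the study could be declared feasible with retention well below 80% because outcomes drifted together. The text does not say so, and on a corroborating reading a missed threshold still blocks the verdict. But the order is left unstated, and the malfunction half of the sentence fails on either reading.

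Secondly, the Research design section includes in its primary question whether the model reliably produces the intended behaviours. This stands: the qualitative stream is partly evidence on implementation, so it would be wrong to say that the matrix carries none. It does not justify requiring BSCS or SSBS change to agree with Tau-U.

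Three further inferences are tempting but unsupported:

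- **A shared absence of change would confirm feasibility.** The preceding sentence gives the matrix's purpose as finding whether the mechanism signal is detectable, which points the other way.
- **The chance that one trait scale's CI misses a true effect is the malfunction rate.** At d = 0.2 that chance is about 73% with 48 completers and 81% with 32. Divergence also needs another stream to show a signal. In addition, the section calls the trait outcome directional and does not require significance testing, so the CI reading is not the obvious one.
- **The matrix cannot be completed because connectedness has no EMA item.** The text describes three streams, not a grid of construct by stream, and the EMA item does supply a state-level estimate.

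**Conclusion.** The concern holds as an unresolved conflict between two stated rules, together with an inference from divergence to malfunction that the protocol's own text undercuts. Because both statements are in the article, its condensed form does not explain the conflict.

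The rule can give wrong verdicts. How often cannot be known from the documents, because they state neither an effect size nor a convergence criterion. The illustrative range for a uniform effect of 0.2 is about 18–34% divergence by sign and 34–61% by CI, over 32 to 48 completers and correlation 0 to 0.5. The finding does not depend on these figures.

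This should be fixed before the study is run or the template reused. It does not undermine the data collection, the sample size or any estimate.

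**What to change.** Replace the last sentence of the Data analysis strategy section proper, before Missing data handling, with:

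> The feasibility verdict rests on the four thresholds alone. The matrix is descriptive evidence on mechanism enactment; convergence does not override a missed threshold, and divergence may reflect sampling error, differing trait and state sensitivity, confounding or implementation, and is not by itself a sign of implementation failure.

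Enactment still enters the verdict through the fidelity threshold, whose third checklist item asks whether the student described a relevant behaviour.

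Optionally, show the paired teacher and parent changes with 95% CIs beside the matrix. The Measures section gives their purpose: "These informant sources provide convergent evidence from ecologically distinct observational contexts, reducing the sole reliance on student self-report". They are not named in any of the three streams.

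The cost is one sentence and, if the option is taken, two descriptive rows from data already planned. No procedure, sample size or measurement changes.
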